### Procedures

For the purpose of this trial we will develop a website to inform potential applicants about the contents of the online treatment, and the procedures associated with this trial. Upon visiting the website, new participants can read all relevant information and ask additional questions through a mail form. For included participants, a secured login system to enter the online interventions is developed and available on the website. Visitors willing to participate fill out a web-based questionnaire to check if they meet the inclusion criteria. If they do not, they are informed so, and an email is sent to this applicant. This email contains additional information about alternative treatment options. Applicants meeting inclusion criteria proceed to the subscription screen. Next, they are once again informed on the conditions of participation in this trial. After reading all information, they decide whether they are willing to participate. If they would like to participate, they are asked for necessary personal information. A confirmation email is sent to them, with the informed consent as an attachment. This confirmation email also contains their personal username and password. With this unique username/password combination, applicants can log in to their private area. Upon logging in for the first time, applicants are shown a screen which requests them to confirm they read, understood and agreed with the informed consent sent to them. Applicants can decide to agree with this informed consent at any time, and can deliberate on whether or not they consent with the participant information for as long as they want. Only after their confirmation they are introduced to the baseline measurement procedure. After completion of the baseline measurement the randomization procedure takes place. Depending on the outcome, participants are allocated to one of three trial arms.

### Trial flow

Figure 1 provides an overview of the trial flow. If a participant is allocated to trial arm 1, he or she is directly introduced to TOA through a welcome text. A notification will now be sent to the TOA coordinator to make a first appointment for a chat session with the participant. From now on, TOA starts for participants in trial arm 1. Three months after t0 measurement, participants will receive an invitation for the t1 measurement by email and upon visiting the trial website. It is possible that some participants have not yet finished the entire TOA process after this period. However, the decision has been made to let follow-up timing depend solely on the time interval since t0, not on the current status of their treatment proceedings. This is in our opinion the best possible confirmation to the 'intention to treat' principle [40]. Three months after the t1 measurement participants are invited for the t2 measurement. After completion of t2 measurements, data collection is completed. Participants in trial arm 2 are introduced to SOA after randomization. Up until t1, participants can use the SOA program every time they log in on the trial website. t1 and t2 measurements are introduced by email and upon visiting the trial website. Participants in this trial arm are offered the possibility to proceed with TOA after completion of t2 measurements, would they be interested in more help after completion of SOA. Participants in trial arm 3 are allocated to the waiting list after randomization. After three months, they too will receive an invitation for the t1 measurement. After t1, participants in trial arm 3 are introduced to TOA. For ethical reasons, the decision is made to offer them TOA after three months (t1), and not after t2 (six months).

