## Methods

### Aims of the trial

This study aims to test the effectiveness and cost-effectiveness of SOA and TOA against a waiting list control group, in a three-arm randomized clinical trial. Primary outcome measure is the change in alcohol consumption from baseline (t0) to the three month follow-up (t1) and to the six month follow-up (t2). Secondary outcome measures are changes in AUDIT scores, quality of life and quality of functioning at work. Incremental cost-effectiveness ratios for SOA and TOA will be calculated. The predictive validity of participant characteristics on treatment adherence and outcome will be explored.

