### Research questions

Q1a. Do TOA participants reduce their alcohol consumption from t0 to t1 and t2 to a larger extent than SOA and waiting list control participants?

Q1b. Do TOA participants improve to a larger extent on secondary outcome measurement scores from t0 to t1 and t2 than SOA and waiting list control participants?

Q1c. Are TOA participants more often treatment-responders than SOA and waiting list control participants at t1 and t2?

Q1d. Do SOA participants reduce their alcohol consumption to a larger extent from t0 to t1 and t2 than waiting list control participants?

Q1e. Do SOA participants improve on secondary outcome measurement scores from t0 to t1 and t2 to a larger extent than waiting list control participants?

Q1f. Are SOA participants more often treatment-responders than waiting list control participants at t1 and t2?

Q2. What are the comparative costs per quality adjusted life year (QALY) for SOA and TOA?

Q3a. How do participants' demographic characteristics relate to demographics of participants in conventional face-to-face CBT programs?

Q3b. Do scores of working alliance between TOA participants and counsellor predict treatment-response at t1 and t2?

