### Data analysis

Multiple imputation missing data handling procedures will be implemented using MICE [45] a package for the R Statistical Software Environment. As the quantity of consumed alcoholic drinks is the primary outcome variable in this trial, analysis techniques are chosen that suit the expected data distribution. Baseline measurements of the three trial arms will be compared using t-tests and χ^2^-tests. Trial arm differences on primary and secondary outcome variables at three months are tested using repeated measures ANOVA. Trial arm differences for SOA and TOA between t1 and t2 are tested with a 2 (group) × 2 (time) repeated measures ANCOVA with between and within contrasts. Effect-sizes will be calculated using Cohen's *d *[46]. Trial arm differences on treatment-response will be tested using multiple logistic regression analysis. Costs from TOA and SOA will be derived from cost records of the collaborating SATC. Costs will be assessed in correspondence to the recommendations by the U.S. Panel on Cost-effectiveness in Health and Medicine [25], following a macro-costing approach. QALYs will be calculated from the EQ-5D questionnaire, using algorithm by Dolan [47], retrieved from the Open Health Measures website [48]. Based on these estimations, costs-per-QALY and an incremental cost-effectiveness ratio can be calculated. The U.S. Panel on Cost-effectiveness has recommended that cost-effectiveness studies should conduct sensitivity analysis, which for this cost-effectiveness analysis will be implemented through the bootstrap method [49-51].

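### At t2 arm 3 is a deferred-TOA arm, yet the aims and Q1a–Q1f still use it as the waiting-list control; the analysis plan leaves this open for treatment response

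*Protocol article*

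**What the plan says.** **Conduct (Trial flow).** "After t1, participants in trial arm 3 are introduced to TOA". This is deliberate and disclosed, on ethical grounds: "the decision is made to offer them TOA after three months (t1), and not after t2 (six months". The second follow-up comes later for everyone: "Three months after the t1 measurement participants are invited for the t2 measurement". SOA participants may move to TOA only once t2 is complete.

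**Aims.** The trial is to "test the effectiveness and cost-effectiveness of SOA and TOA against a waiting list control group", and the primary outcome is change in consumption from baseline "to the three month follow-up (t1) and to the six month follow-up (t2".

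**Research questions.** Each of Q1a to Q1f names both t1 and t2 and has the waiting list as a comparator. On consumption, Q1a asks: "Do TOA participants reduce their alcohol consumption from t0 to t1 and t2 to a larger extent than SOA and waiting list control participants". On response, Q1f asks: "Are SOA participants more often treatment-responders than waiting list control participants at t1 and t2". Q1c asks the same for TOA.

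**Outcomes.** The section on primary and secondary outcome measures counts treatment response as a primary outcome alongside consumption. Its definition measures the deterioration component from t0 to t1. Relative risk reduction, number needed to treat and odds ratios are to be derived from it.

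**Hypotheses and Data analysis.** For consumption and secondary outcomes, the waiting-list contrasts are placed at t1, and the three-arm ANOVA is at three months. From t1 to t2, only SOA and TOA are compared. For response, the hypotheses give no time point, and the model is described in one sentence: "Trial arm differences on treatment-response will be tested using multiple logistic regression analysis".

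**The concern.** By t2, arm 3 has had three months of access to one of the two treatments under test. It can no longer stand for what happens without treatment. A t2 contrast of arm 1 with arm 3 compares immediate with deferred TOA. A t2 contrast of arm 2 with arm 3 compares SOA with deferred TOA. Neither answers the question put in Q1a to Q1f, which describe arm 3 as a control at both times.

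The stake is a primary outcome. If Q1c and Q1f are answered as written, the report would carry t2 odds ratios and numbers needed to treat labelled as effects against a waiting list. If TOA works and arm 3 takes it up, the TOA figure would be pulled towards no difference. The SOA figure could suggest no benefit, or a disadvantage, even if SOA does better than no treatment.

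**Working it through.** **1. Which outcomes are exposed**

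| Outcome | Research questions | Hypotheses | Data analysis |
|---|---|---|---|
| Consumption (Q1a, Q1d) | waiting list at t1 and t2 | waiting list at t1; SOA–TOA from t1 to t2 | three arms at three months; SOA–TOA from t1 to t2 |
| Secondary outcomes (Q1b, Q1e) | waiting list at t1 and t2 | waiting list, t0 to t1 | three arms at three months; SOA–TOA from t1 to t2 |
| Treatment response (Q1c, Q1f) | waiting list at t1 and t2 | no time point | logistic regression, no time point, no restriction of arms |

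In the first two rows the aims and research questions contradict the hypotheses and the analysis. In the third row nothing in the analysis restrains the t2 question. The definition of response ties only its deterioration component to t0–t1; the drinking-limit component is not tied to a visit.

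**2. The plan's own figure**

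Table 3 reproduces. With N = 159 and f = 0.25, λ = N·f² = 159 × 0.0625 = 9.9375, critical F(2, 156) = 3.054 and power is 0.805. This point does not depend on that figure.

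**3. How far a t2 contrast with arm 3 could move (illustration)**

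Inputs from Power calculation and Randomization: d = 0.40 for waiting list against treatment, 0.25 between SOA and TOA (called d in the text; Table 3 enters 0.25 as f), and 50 per arm. Assumptions not in the document: r, the share of the TOA effect that arm 3 has gained by t2; effects maintained to t2; and how 0.40 and 0.25 are assigned to the two treatments.

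- TOA − arm 3 = d_TOA × (1 − r)
- SOA − arm 3 = d_SOA − r × d_TOA

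TOA against arm 3 with d_TOA = 0.40 (two-sided 0.05, noncentral t, 50 per arm):

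| r | contrast | power |
|---|---|---|
| 0 | 0.40 | 51% |
| 0.25 | 0.30 | 32% |
| 0.5 | 0.20 | 17% |
| 0.75 | 0.10 | 8% |
| 1 | 0 | 5% (alpha) |

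SOA against arm 3, under three ways of assigning the effects:

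| d_TOA, d_SOA | r = 0 | r = 0.5 | r = 1 |
|---|---|---|---|
| 0.40, 0.40 | 0.40 | 0.20 | 0 |
| 0.65 (0.40 + 0.25), 0.40 | 0.40 | 0.075 | −0.25 |
| 0.40, 0.15 (0.40 − 0.25) | 0.15 | −0.05 | −0.25 |

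The SOA contrast changes sign when r exceeds d_SOA/d_TOA: 0.40/0.65 = 0.62 in the second row, 0.15/0.40 = 0.375 in the third, and never in the first. The Hypotheses section expects SOA drinking to rise between t1 and t2, which would lower d_SOA at t2 and move the contrast further down.

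These are standardised mean differences. The document gives no responder proportions, so the odds ratio and number needed to treat cannot be computed from it; only the direction carries over.

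**The case against.** The strongest reply is that the authors have already dealt with most of this. The Hypotheses section places the waiting-list contrasts for consumption and secondary outcomes at t1. The Data analysis section tests three arms at three months and then only SOA against TOA. That stands: no t2 waiting-list test of those outcomes is planned, and for them only the wording of the aims and research questions is at fault.

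It can also be said that the time point of one regression is detail that a condensed article leaves to the full protocol or analysis plan, and that the t0–t1 deterioration component suggests response was meant for t1. The first part would hold if the article were silent. It is not: Q1c and Q1f name t2 with the waiting list as comparator. The second narrows the gap but does not close it.

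Stronger readings are tempting and are not supported:

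- A reader might infer that every t2 comparison with arm 3 is invalid. It is a valid randomised comparison of immediate TOA, or SOA, with deferred TOA; it fails only as an effect against no treatment.
- A reader might infer that the trial has no controlled information at six months. SOA versus TOA is randomised, and by design SOA participants are not offered TOA until t2 is complete.
- A reader might take 0.65 and 0.40 as the document's own effects against no treatment and sign reversal as its implication. The document gives 0.40 for treatment in general; the sum of 0.65 is constructed here, and under it the SOA contrast is still +0.075 at r = 0.5.

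**Conclusion.** The point holds in a limited form. At t2 arm 3 is a deferred-TOA arm, so the t2 waiting-list comparisons in the aims and Q1a to Q1f do not estimate an effect against no treatment. For consumption and secondary outcomes this is an internal contradiction, because the hypotheses and analysis already stop at t1. For treatment response it is a live error in a primary outcome: the t2 question is asked and the model is not limited.

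That conclusion rests on the documents alone. Its size does not. TOA against arm 3 would shrink towards no difference as r rises, for example from d = 0.40 to 0.20 at r = 0.5, with power at 50 per arm going from 51% to 17%. SOA against arm 3 could stay positive, be near zero or reverse, depending on r and on the assumed effects. The timing of TOA for arm 3 is not questioned.

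**What to change.** 1. In the aims and in Q1a to Q1f, restrict every comparison with the waiting list to t1 and keep t2 for SOA versus TOA. This brings them into line with the Hypotheses and Data analysis sections.
2. In Data analysis, specify the treatment-response regression as three arms at t1 and SOA versus TOA at t2. State the time point in the response hypotheses, and say which interval the deterioration component uses for a t2 response.
3. Label any t2 contrast with arm 3 as immediate TOA, or SOA, versus deferred TOA, and do not report an odds ratio or number needed to treat from it as an effect against a waiting list.
4. State that the trial gives no waiting-list-controlled effect at six months, while SOA versus TOA remains a randomised comparison then.

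The cost is wording in the aims, research questions, hypotheses, response definition and analysis section. Recruitment, allocation, treatment and data collection do not change. The edits should be made before the analysis.

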**Figure 1 F1:**
[figure not shown]
**Trial flowchart**. This figure provides an overview of the participant flow for this trial.

### Maximize response rates

Drop-out is a potential threat in every clinical trial. Since attrition rates for online trials tend to be larger than in regular ones [52], we will make extra efforts to maximize response rates. Following suggestions for successful strategies to maximize response rates [41,42], we made follow-up questionnaires as short as possible and give participants feedback on the actual length and their proceedings while filling out the questionnaire. We motivate participants to fill out the questionnaires by sending them a reminder if they do not respond within five days after the first emailed invitation. To optimize a feeling of worthiness and to reward participants for their efforts and time, participants will receive gift coupons (€15,-) after filling out a follow-up questionnaire. Participants will be aware of this incentive upon reading the informed consent form. However, participants who do not fill out the questionnaires after a reminder is sent will be contacted by a call centre. Since 2005, this call centre has been collecting regular outcome data of outpatient addiction treatment for SATCs nationwide in the Netherlands. It is experienced in maximizing response rates in hard to reach populations [43]. For this research project, they will collect outcome data by phone from trial participants who do not respond to emailed invitations. All participants are aware of these procedures, provide phone numbers, and consent with receiving phone-calls for follow-up measurements.

### Data analysis

Multiple imputation missing data handling procedures will be implemented using MICE [45] a package for the R Statistical Software Environment. As the quantity of consumed alcoholic drinks is the primary outcome variable in this trial, analysis techniques are chosen that suit the expected data distribution. Baseline measurements of the three trial arms will be compared using t-tests and χ^2^-tests. Trial arm differences on primary and secondary outcome variables at three months are tested using repeated measures ANOVA. Trial arm differences for SOA and TOA between t1 and t2 are tested with a 2 (group) × 2 (time) repeated measures ANCOVA with between and within contrasts. Effect-sizes will be calculated using Cohen's *d *[46]. Trial arm differences on treatment-response will be tested using multiple logistic regression analysis. Costs from TOA and SOA will be derived from cost records of the collaborating SATC. Costs will be assessed in correspondence to the recommendations by the U.S. Panel on Cost-effectiveness in Health and Medicine [25], following a macro-costing approach. QALYs will be calculated from the EQ-5D questionnaire, using algorithm by Dolan [47], retrieved from the Open Health Measures website [48]. Based on these estimations, costs-per-QALY and an incremental cost-effectiveness ratio can be calculated. The U.S. Panel on Cost-effectiveness has recommended that cost-effectiveness studies should conduct sensitivity analysis, which for this cost-effectiveness analysis will be implemented through the bootstrap method [49-51].

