### Randomization

After the t0 measurement is completed, participants are allocated to one of the three trial arms. Because this randomized clinical trial is internet-based, we will organize the allocation procedures online as well. As the number of participants we aim to include in each trial arm (*n *= 50) is not very large, random variation in baseline characteristics could reduce group equivalence. Online, server-based performance of randomization procedures comes with the advantage of being able to implement stratified allocation or allocation through adaptive randomization relatively easy.

To prevent between-group variability on relevant baseline characteristics, we use an adaptive or biased-coin randomization algorithm for this trial. Adaptive randomization aims to ensure trial arms are balanced with respect to a priori defined participant factors as well as for the number of participants in each group. Simulation studies show that adaptive randomization provides better balanced trial arms when compared with 'normal' randomization [35] and that it is more efficient in balancing multiple poli-level factors than permutated block stratification [36]. Although not widely used due to organizational complexity, adaptive randomization is a highly effective allocation method, and its wider adaptation in the conduct of randomized clinical trials is recommended [37]. The use of adaptive randomization is supported in the CONSORT statement [38]. We will implement the Pocock & Simon Range Method of adaptive randomization [39], with D = 'range', G is the sum of D (no factor weighting), and P = 0.60.

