A second potential risk in this trial would concern the inclusion of participants. The inclusion of enough participants is not our main sorrow. As SOA in the regular context and without promotional efforts is able to attract over 150 new participants each month [6], we think we will manage to include 150 participants in a one year inclusion period. However, the resemblance of the regular online clientele is our main focus of attention. Due to the high accessibility of online help in the normal context and the relatively high constraints posed on participants in this trial, there is a potential risk that the trial participants do not resemble the regular e-clientele exactly. Whether this actually occurs or not can only be answered afterwards, by comparing data on characteristics of trial participants and regular online clientele data.

A third possible limitation concerns integrity of our collected data. As our t0 and t1/t2 data is self reported without a researcher nearby to oversee data-collection, we rely heavily on the correctness of our participants' answers. Various authors evaluate the self-reported data in alcohol research as reliable [53-55]. Tourangeau and colleagues even concluded that self-reported data is more reliable in the absence of a research confederate [56]. However, as an extra means to check data integrity, we included a social desirability scale, to measure whether these tendencies occur in our research population.

Another point of concern on data integrity in this trial could be made about our suggested statistical procedures. Multivariate statistics relies considerably on data distribution normality [57]. As the distribution of alcohol consumption count data is usually zero-elevated and highly skewed, particularly in subjects with alcohol dependence [58], multivariate statistics and most statistical tests should be used with caution. To prevent possible in- or deflated α's, we will use bootstrap methods and permutation tests as suggested by Hesterberg and colleagues [59], to minimize the influence of data distributions on our testing results, if data turn out to be non-normally distributed.

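### The three-month repeated measures ANOVA amounts to a change-score test; ANCOVA on the baseline value and the minimisation factors would be more precise and needs no new data

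*Protocol article*

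**What the plan says.** - **Three-month test** (Data analysis): "Trial arm differences on primary and secondary outcome variables at three months are tested using repeated measures ANOVA". No covariate is named. The Hypotheses section places the main efficacy hypotheses (Q1a, Q1d) at t1, so this is the key test.
- **Later test** (same section): "Trial arm differences for SOA and TOA between t1 and t2 are tested with a 2 (group) × 2 (time) repeated measures ANCOVA". The article therefore does use ANCOVA, but only for SOA against TOA after t1, and its covariates are not named.
- **Primary outcome** (Aims of the trial): change in alcohol consumption from t0 to t1 and to t2.
- **Allocation** (Randomization): "To prevent between-group variability on relevant baseline characteristics, we use an adaptive or biased-coin randomization algorithm for this trial". The method is Pocock and Simon, "with D = 'range', G is the sum of D (no factor weighting), and P = 0.60". The purpose is stated as: "Adaptive randomization aims to ensure trial arms are balanced with respect to a priori defined participant factors". The article does not name the factors and does not say that they enter the analysis.
- **Distribution** (Discussion): "As the distribution of alcohol consumption count data is usually zero-elevated and highly skewed". Bootstrap and permutation methods are to be used "if data turn out to be non-normally distributed".
- **Sample size** (Power calculation, Table 3; Randomization): a one-way ANOVA with three groups, f = 0.25, N = 159 and power 0.805. The recruitment target is 150, or 50 per arm. The text expects d = 0.40 for treatment against waiting list.

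**The concern.** The trial measures consumption before allocation and balances the arms on factors it regards as relevant, but the three-month model makes limited use of either.

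A change score fixes the coefficient of the baseline value at 1 instead of estimating it. Unless that happens to be the right slope, it adds noise.

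Factors that were deliberately balanced, if they predict the analysed variable, make the true spread of the arm difference smaller than an unadjusted model believes. The standard error is then too large.

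What is at stake is precision: power on the pairwise contrasts, which is modest with 50 per arm, and the width of the confidence intervals. A smaller matter is that the article expects skewed data with many zeros, yet names a normal-theory test and leaves the move to resampling until the data have been seen.

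**Working it through.** **1. The plan's own figure.** One-way ANOVA with f = 0.25, three groups, N = 159:
- λ = N·f² = 159 × 0.0625 = 9.9375
- critical F(2, 156) = 3.054
- power 0.805

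This agrees with Table 3. At the target of 150, λ = 9.375 and power is 0.780. This calculation contains no t0–t1 correlation.

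**2. What the planned test is.** With two time points, the group-by-time F test is the one-way ANOVA of (t1 − t0). Write s0 and s1 for the SDs at t0 and t1, and r for their correlation.
- Change-score error variance: s1² + s0² − 2·r·s0·s1
- ANCOVA error variance: s1²·(1 − r²)
- Difference: s0² − 2·r·s0·s1 + r²·s1² = (s0 − r·s1)², which is never negative

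So apart from one degree of freedom, ANCOVA is never the less precise of the two, whatever the SDs. With equal SDs set to 1, the variances are 2(1 − r) and 1 − r², and their ratio is (1 + r)/2.

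**3. Pairwise power.** Inputs: 50 per arm (Randomization), d = 0.40 (Power calculation) taken as standardised on the t1 SD, two-sided 5%, noncentral t. The value of r is assumed, because the article gives none. The effective d is 0.40/√(error variance).

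| r (assumed) | Change variance | ANCOVA variance | Ratio | Effective d, change | Effective d, ANCOVA | Power, change | Power, ANCOVA |
|---|---|---|---|---|---|---|---|
| 0.3 | 1.40 | 0.91 | 0.65 | 0.338 | 0.419 | 0.39 | 0.55 |
| 0.5 | 1.00 | 0.75 | 0.75 | 0.400 | 0.462 | 0.51 | 0.63 |
| 0.7 | 0.60 | 0.51 | 0.85 | 0.516 | 0.560 | 0.72 | 0.79 |

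**4. Omnibus power, N = 150, f = 0.25, same rescaling.** Change score against ANCOVA: 0.625 against 0.819 (r = 0.3), 0.780 against 0.890 (r = 0.5), 0.948 against 0.975 (r = 0.7). Below r = 0.5 the planned test is weaker than the one-way ANOVA on which the trial was sized (0.780).

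**5. Omitted minimisation factors.** Suppose the factors explain a share R² of the variance *of the change score*. With near-complete balance, the model standard error is too large by 1/√(1 − R²), and the nominal 5% test has size 2·[1 − Φ(1.96/√(1 − R²))].

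| R² (assumed) | SE inflation | Actual size |
|---|---|---|
| 0.10 | 1.05 | 3.9% |
| 0.20 | 1.12 | 2.8% |
| 0.30 | 1.20 | 1.9% |

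Balance is not complete with P = 0.60, so the article's scheme was simulated: range, unweighted sum, three arms, N = 150, three assumed binary factors, 2,000 null trials per setting. The test rejected 4.1%, 2.9% and 2.0% of the time. With the factors in the model it rejected 5.4–5.6%. Other runs with different seeds and layouts fell between about 3% and 5% at R² = 0.10 and between about 1.5% and 2% at R² = 0.30, so these sizes are good to about one percentage point.

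**6. When step 5 does not apply.** A factor that shifts t0 and t1 equally cancels from t1 − t0. In that case R² for the change score is 0 and the size is 5%, however strongly the factor predicts the level of drinking at t1.

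**The case against.** **The planned test is valid for the stated outcome.** The primary outcome is defined as change, and under randomisation the group-by-time test is an unbiased test of it. This stands, so the point is one of efficiency. Changing to ANCOVA does not change the question: the adjusted difference at t1 and the difference in change estimate the same arm effect.

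**Baseline is not ignored.** Correct. It is in the model as the first time level. It is not there as a covariate, and that is where precision is lost.

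**An article may leave covariates to a fuller plan.** This stands for the names of the minimisation factors, and their absence is not a finding. It carries less weight for the model itself. The article names ANOVA for three months and ANCOVA for the later comparison, so the three-month model is a stated choice.

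**The sizes rest on figures the article does not give.** This stands. The power figures need r, equal SDs and d on the t1 SD scale. If d = 0.40 is already on the change scale, the starting power is 0.51 at every r, and the variance ratio is unchanged. At r = 0.7 the gain is only about 7 points.

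**Stronger readings that the article does not support.**
- A reader might infer that the standard errors are wrong as a matter of fact. That depends on whether the unnamed factors predict change, and the effect could be nil.
- A reader might infer a risk of false positives. Any error here is conservative.
- A reader might infer that the response analysis is unadjusted. The article calls that logistic regression multiple, so it may already carry covariates.
- A reader might infer that resampling is an afterthought. The article names the methods and the trigger in advance; what stays open is that the trigger depends on the observed data.

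**Conclusion.** The point holds as a matter of efficiency, with a conditional addition on standard errors.

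- **Firm:** the three-month test is a change-score comparison, and ANCOVA on the same data has an error variance that is no larger. With equal SDs the ratio is (1 + r)/2.
- **Dependent on assumed r, equal SDs and d = 0.40 on the t1 SD scale:** pairwise power with 50 per arm rises by about 16 points at r = 0.3, 12 at r = 0.5 and 7 at r = 0.7.
- **Conditional on the factors predicting change:** omitting them makes the nominal 5% test run at about 4% to 2% when they explain 10–30% of change-score variance. Otherwise there is no effect.

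The planned analysis is not invalid and does not inflate type I error. The change should be made because it recovers power in a trial whose pairwise contrasts have little to spare, and because the article itself expects the distribution that would trigger its fallback.

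**What to change.** 1. In Data analysis, replace the three-month repeated measures ANOVA with ANCOVA of the t1 value on arm, the t0 value of the same outcome and the factors used in the Pocock and Simon allocation. Apply this to the primary consumption outcome and to the continuous secondary outcomes.
2. State in advance that p-values and confidence intervals for this model come from the bootstrap, or from a re-randomisation test that replays the minimisation in the recorded order of entry with the recorded settings. A simple permutation of arm labels would not reflect the way participants were allocated.

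The cost is analysis wording only. The baseline values and allocation factors are collected before allocation. The re-randomisation option also needs the server's allocation sequence to be kept. Sample size, visits and instruments are unaffected.
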